***Introduction***. Postpartum depression (PPD) and sub-clinical PPD affect approximately 8 to 15% of Canadian women following childbirth (Chalmers et al., 2008). The disorder is debilitating and impacts a woman’s quality of life and her ability to care for and connect with her infant. PPD is also related to short- and long-term consequences for the infant (Tronick & Reck, 2009). Unfortunately, PPD is undertreated for reasons including lack of access to providers and limited mobility. Using the internet to deliver therapy is an innovative way to improve access to psychological treatment. Evidence has suggested that internet cognitive behavior therapy (ICBT) results in significantly larger effect sizes compared to all other online interventions (Barak et al., 2008) and that therapist-assisted ICBT (TAICBT) is comparable to in-person CBT (Spek, 2007).While there is evidence to support the efficacy of TAICBT for the treatment of major depression (Cuijpers et al., 2010), to date, researchers have yet to determine whether this modality is efficacious for the treatment of PPD.

***Purpose and Hypotheses****.* The proposed study will determine whether TAICBT is more efficacious than a waitlist control (WLC) condition in reducing depressive symptom severity, anxiety, general stress, parental stress, and for improving quality of life for women with PPD. It is hypothesized that TAICBT participants will demonstrate significantly greater symptom and clinical improvement from pre- to post-treatment on all outcome measures. It is also expected that symptom improvements will be maintained four weeks following the conclusion of treatment. Given that the TAICBT has not been examined in PPD populations, treatment expectancy, satisfaction, and therapeutic alliance will also be investigated. It is hypothesized that: (a)TAICBT participants will report satisfaction with the treatment,(b) significant associations will be revealed between post-treatment therapeutic alliance ratings and symptom changes scores, and (c) treatment expectancy and satisfaction will be moderately correlated with symptom change scores on all outcome measures. To further understand the participants’ experience with TAICBT, ten open-ended questions will be asked.

***Method****.* Using a randomized controlled design, 58 women will be randomized to receive either TAICBT treatment or assigned to a 7-10 week WLC. Participants assigned to the WLC will receive a pamphlet that includes information on information on PPD and websites for support services offered in Saskatchewan. The intervention will consist of a seven-module TAICBT program adapted for women afflicted with PPD. Each TAICBT participant will be assigned to a therapist who they can correspond with weekly via email. Potential participants will be screened using the **Edinburgh Postnatal Depression Scale** (EPDS; Cox et al., 1987), modules from the **MINI International Neuropsychiatric Interview** (Sheehan et al., 1998), as well as standard screening questions. If deemed eligible, the following additional outcome measures will be administered: (a)**Depression Anxiety Stress Scale- Short Form** (DASS; Lovibond & Lovibond, 1995) to measure levels of depression, stress, and anxiety; (b)**Parenting Stress Index- Short Form** (PSI-SF; Abidin, 1995) to assess stress in the parent-child system; (c) **World Health Organization Quality of Life – BREF** (WHOQOL-BREF; WHOQOL Group, 1998) to assess quality of life;(d) **Therapist Alliance Questionnaire** (TAQ; Kiropoulos et al., 2008, modified from Luborsky’s 1985 HAQ-II) to determine the degree to which participants perceive the relationship with their therapist as helpful; (e) **Treatment Satisfaction Questionnaire-Modified** (TSQ; Cox et al., 1994) to assess the client’s perceived satisfaction with treatment; and (f) **Credibility/Expectancy Questionnaire**(CEQ; Devilly & Borkovec, 2000) to measure credibility and treatment expectancy of the TAICBT treatment. The TAQ, TSQ, and CEQ will only be completed by those participants receiving TAICBT treatment. All other measures will be completed by both groups of participants at pre-treatment and post-treatment (10 weeks after baseline). Following the 7-10 week wait, participants in the WLC group will be contacted, re-screened, and if still eligible, they will be offered the treatment. At this time, the TAICBT participants will be asked to respond to ten open-ended questions regarding their experiences with the program. To provide a longer-term follow-up of depressive symptoms, TAICBT participants will be contacted by telephone four weeks following treatment completion and administered the EPDS and the depression module of the MINI.

***Analysis****.* Means, standard deviations, and ranges of all scores for all pre- and post-treatment measures will be computed. Independent samples *t*-tests and chi-square tests will be conducted to assess for group differences in demographic data and baseline measures. Treatment efficacy will be determined using repeated measures mixed-model analysis of variances (ANOVAs). Eta square effect sizes will be computed for all outcome measures. The Jacobson and Truax (1991) method will be used to discern clinical significance, and remission and recovery rates will be reported for both groups. Mixed-model ANOVAs along with tests of simple effects and interaction contrasts will be computed to determine if the TAICBT group maintained the expected treatment gains. The open-ended questions will be analyzed using a grounded theory approach.

***Discussion.*** If found effective, the TAICBT program for PPD could benefit not only Saskatchewan mothers’ mental health and quality of life, but also their infants’ physical and psychological health and the family environment.

5. Researcher Qualifications: Describe any special training or qualifications you and/or the research team have - only in cases where the research involves special or vulnerable populations (e.g. children, incarcerated individuals, etc), distinct cultural groups, or the research is above minimal risk, otherwise this section may be omitted.

N/A

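### No primary outcome and no rule for efficacy: the hypothesis spans all outcome measures, and depression is scored on both the EPDS and the DASS-21

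*Protocol*

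**What the plan says.** The Purpose and Hypotheses paragraph asks whether TAICBT is better than a waitlist "in reducing depressive symptom severity, anxiety, general stress, parental stress, and for improving quality of life for women with PPD". These are five domains in one list, none marked as the main one. The efficacy hypothesis is that "TAICBT participants will demonstrate significantly greater symptom and clinical improvement from pre- to post-treatment on all outcome measures".

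The Method paragraph screens with the EPDS and MINI and then says that "the following additional outcome measures will be administered". Of these, the DASS is given "to measure levels of depression, stress, and anxiety", the PSI-SF "to assess stress in the parent-child system", and the WHOQOL-BREF for quality of life. Three questionnaires (TAQ, TSQ, CEQ) are for the TAICBT arm only. For the rest, "All other measures will be completed by both groups of participants at pre-treatment and post-treatment (10 weeks after baseline"). Four weeks after treatment, TAICBT participants are "administered the EPDS and the depression module of the MINI".

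The Analysis paragraph states: "Treatment efficacy will be determined using repeated measures mixed-model analysis of variances (ANOVAs"). It does not say which score carries the conclusion. The available text states no significance level and no sidedness.

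**The concern.** A trial that asks whether a treatment works needs to say in advance which comparison answers the question. Here the word efficacy could mean that every score improved significantly, that any score did, or that one of the two depression scores did. The protocol does not choose.

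The two depression scores make this concrete. If the EPDS favours TAICBT and the DASS-21 depression score does not, or the reverse, the same data support either conclusion, and the choice would be made after the results are known. For a trial in postpartum depression, that is the central question.

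**Working it through.** **Inputs from the protocol.** 58 women are randomised (Method). The scores compared between arms are EPDS (1), DASS-21 depression, anxiety and stress (3), PSI-SF (at least 1) and WHOQOL-BREF (at least 1): 1 + 3 + 1 + 1 = 6.

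**Assumptions, none stated in the protocol.** Two-sided 5% per test; 1:1 allocation, so 58/2 = 29 per arm; no dropout; the same standardised difference d on every score, in SD units of the quantity compared; the same correlation r between every pair of test statistics; normal approximation.

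**The plan's own figure.** The 58 cannot be reproduced, because no error rate, power, effect size or SD accompanies it. It can only be inverted: 29 per arm gives 80% power at d = (1.960 + 0.842) × √(2/29) = 0.74.

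**If any one score suffices.** With independent scores, the chance of at least one false positive is 1 − 0.95⁶ = 0.265. In favour of TAICBT only, it is 1 − 0.975⁶ = 0.141.

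**If every score must be significant.** At d = 0.75 the test statistic has mean 0.75/√(2/29) = 2.856, so one score has power Φ(2.856 − 1.960) = 0.815. Six independent scores give 0.815⁶ = 0.293.

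**With correlation.** Six equicorrelated test statistics were simulated (400,000 draws):

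| r | Any of six false, either direction | Any of six false, favouring TAICBT | All six significant, d = 0.75 | All six significant, d = 0.5 |
|---|---|---|---|---|
| 0 | 26.5% | 14.1% | 29.4% | 1.2% |
| 0.3 | 24.1% | 12.2% | 42.3% | 7.0% |
| 0.5 | 20.7% | 10.3% | 50.4% | 12.7% |
| 0.7 | 16.4% | 8.2% | 59.0% | 20.5% |
| One score only | 5% | 2.5% | 81.5% | 47.8% |

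Under the all-six rule, with no effect on any score, the chance that all six are significant is 0.3% or less for r up to 0.7. That reading costs power and inflates no error.

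**Keeping six co-equal scores instead.** Bonferroni at 0.05/6 = 0.00833 raises the difference detectable at 80% power from d = 0.74 to d = 0.91.

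**Is the EPDS available as a primary outcome?**
- The Method paragraph calls the DASS, PSI-SF and WHOQOL-BREF additional outcome measures and has everything but the three TAICBT-only questionnaires completed before and after treatment. This implies that the EPDS is included.
- Section III, question 6(c), gives therapists access to outcome measures at the start and end of treatment, partly to monitor EPDS item 10. This points the same way.
- Section III, question 3, cites only Appendices H to M for the baseline and post-treatment batteries. The EPDS is Appendix C.
- On timing, Method places post-treatment 10 weeks after baseline. The Pamphlet Condition text in Section III places it seven to ten weeks after baseline for controls. The TAICBT text there places it after treatment completion.

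**The case against.** The strongest reply is that the hypothesis is a directional expectation rather than a decision rule, and that alpha, multiplicity adjustment and order of testing commonly sit in a statistical analysis plan, which may exist and is not shown. The second part stands: the absence of a multiplicity procedure is not a finding here. The first part does not remove the problem, because if the sentence is not a decision rule, the protocol has none. Which outcome answers the trial's question belongs in the protocol.

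A reader might infer that the trial tests six scores at 5% each and so has an inflated error rate. The documents do not support that. No alpha is given, separate ANOVAs per score are inferred from the plural, and the literal wording, which requires all measures, inflates nothing. The 26.5% also assumes independence, which is unlikely for an EPDS score and three DASS scores from the same women, and it counts errors in both directions.

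It is also fair to say that the scales are not wholly co-equal. Depressive symptoms come first in the purpose, the EPDS helps define eligibility (Section III, question 1), and it is the only symptom scale carried to the four-week follow-up. The DASS may be there chiefly for anxiety and stress. This supports the EPDS as the choice, but it falls short of designating it.

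Finally, a reader might infer from the appendix references that the EPDS is not collected after treatment. The Method paragraph and question 6(c) point the other way, so its collection is unclear rather than absent.

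**Conclusion.** The point holds as a badly fixed objective. The protocol hypothesises significance on every outcome measure, judges efficacy by several analyses, scores depression twice and gives no rule for what counts as efficacy.

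The size depends on a reading that the protocol leaves open. Under an any-score reading, the false-positive chance is 16% to 26.5% for r from 0.7 to 0, or about 8% to 14% in favour of TAICBT. Under the literal all-scores reading, power falls from about 81% to between 29% and 59% at d = 0.75. These figures rest on the assumed two-sided 5%; the power figures also assume 29 per arm without dropout and an equal effect on every score. Six is a minimum count. If WHOQOL-BREF were analysed as four domain scores (a further assumption), there would be nine, and the any-score range would be 20% to 37%.

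The documents support neither a claim of actual error inflation nor a complaint about missing multiplicity adjustment.

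**What to change.** - Name one primary outcome: the EPDS total at post-treatment, compared between arms with adjustment for baseline EPDS. The planned mixed-model ANOVA is not an error. But with two time points its group-by-time test is a comparison of change scores, and under randomisation baseline adjustment is at least as precise when variances are equal: the variance ratio is (1 + ρ)/2, where ρ is the pre-post correlation.
- State alpha and sidedness for that test.
- Make DASS-21, PSI-SF and WHOQOL-BREF secondary, and reword the efficacy hypothesis to match. Handling of multiplicity among them can stay in the statistical analysis plan.
- List the EPDS explicitly in the pre- and post-treatment batteries in Section III, question 3.
- Reconcile the post-treatment time point for both arms between Method and Section III.

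At an assumed two-sided 5%, the main question then carries a 5% error rate. Power with 29 per arm is about 48% at d = 0.5, 81% at 0.75 and 86% at 0.8 by the normal approximation (47%, 80% and 85% by noncentral t).

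The cost is protocol wording, plus confirmation that the EPDS is administered at both visits. The downside is that an isolated secondary finding could no longer be claimed as proof of efficacy.

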APPENDIX K. THE THERAPEUTIC ALLIANCE QUESTIONNAIRE (TAQ)^[[7]](#footnote-7)^

There are ways that a person may feel or react in relation to another person. Consider carefully your relationship with your therapist, and then place a score in the rating column (based on the scale below), according to how strongly you agree or disagree. Please score every one.

| Strongly disagree | Disagree | Slightly Disagree | Slightly Agree | Agree | Strongly Agree |
| --- | --- | --- | --- | --- | --- |
| 1 | 2 | 3 | 4 | 5 | 6 |

|  | *Question* | Rating (0-6) |
| --- | --- | --- |
| 1 | I found I was able to rely on my therapist. | _______ |
| 2 | I felt my therapist understood those concerns that were important to me. | _______ |
| 3 | I felt my therapist was helping me to achieve my goals. | _______ |
| 4 | My therapist and I worked well together throughout the treatment program. | _______ |
| 5 | I believe that my therapist and I viewed my concerns in a similar way. | _______ |
| 6 | I felt comfortable with my therapist’s ability to guide me through the program. | _______ |
| 7 | I believe that the techniques used in the program were beneficial. | _______ |
| 8 | I developed a respect for my therapist. | _______ |
| 9 | I felt that my therapist and I were able to communicate effectively. | _______ |
| 10 | Our communications seemed to slow my treatment progress. | _______ |
| 11 | I regarded my therapist’s view about me. | _______ |
| 12 | I felt that I developed a good relationship with my therapist. | _______ |
| 13 | My therapist appeared to be competent in helping people. | _______ |
| 14 | I had meaningful communications with my therapist. | _______ |
| 15 | At times, I had fruitless exchanges with my therapist. | _______ |
| 16 | I believed the therapist respected me. | _______ |
| 17 | At times, I felt that my therapist appeared distant. | _______ |

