**Not at A little Somewhat Quite A lot Very much**

**all so**

**Rating (0-7)**

| 1. How much do you think you improved with respect to depression symptoms? | __________ |
| --- | --- |
| 1. How much do you think you improved with respect to the frequency of your depressed mood symptoms? | __________ |
| 1. How much do you think you improved with respect to the severity of your depressed mood? | __________ |
| 1. How much do you think you improved with respect to identifying your negative thoughts and feelings? | __________ |
| 1. How much do you think you improved with respect to your overall mood? | __________ |

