**Rating (0-7)**

| 1. How do you think your life has improved with respect to your participation in leisure activities? | __________ |
| --- | --- |
| 1. How do you think your life has improved with respect to your participation in family activities? | __________ |
| 1. How do you think your life has improved with respect to your participation in social activities? | __________ |
| 1. How do you think your life has improved with respect to your ability to be alone? | __________ |

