**General Comments:**

1. What was the best part of the program? ________________________________________
2. What was the worst part of the program? ________________________________________
3. How could the program be improved? __________________________________________

Overall, how much improvement do you believe occurred, after completing the treatment program? (Please Circle)

| 0 1 2 3 4 5 6 7 8 9 10  **No Improvement Most Improvement**  **at All Possible** |
| --- |

1. How many hours did you spend in total reading and re-reading the content in the Maternal Depression Online Program?

Please circle one

1-5 hours 6-11 hours 12-17 hours 17-23 hours 24-29 hours 30 hours or Over

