APPENDIX M. CREDIBILITY/EXPECTANCY QUESTIONNAIRE (CEQ)^[[9]](#footnote-9)^

We would like you to indicate below how much you believe, *right now*, that the therapy you are receiving will help to reduce your anxiety. Belief usually has two aspects to it: (1) what one *thinks* will happen and (2) what one *feels* will happen. Sometimes these are similar; sometimes they are different. Please answer the questions below. In the first set, answer in terms of what you *think*. In the second set answer in terms of what you really and truly *feel*. Your therapist will not see these ratings.

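### The TSQ mixes liking of the program with self-rated improvement, so a satisfaction-change correlation based on the whole form would partly reflect shared content; two form wordings also need correcting

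*Protocol*

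**What the plan says.** The Purpose and Hypotheses paragraph expects, as hypothesis (a), that treated women will report satisfaction. Hypothesis (b) expects alliance ratings to be associated with symptom change, and hypothesis (c) expects that "treatment expectancy and satisfaction will be moderately correlated with symptom change scores on all outcome measures". The Method paragraph introduces the TSQ as the measure of "perceived satisfaction with treatment". It singles out no part of the form, and it states that the TSQ, the alliance questionnaire (TAQ) and the Credibility/Expectancy Questionnaire (CEQ) are completed in the TAICBT arm only.

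The forms are printed in the appendices.

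- **TSQ (Appendix L).** Parts A and B ask how useful and how well liked the components were. Part C asks about improvement in depression, for example "How much do you think you improved with respect to depression symptoms" and "How much do you think you improved with respect to the severity of your depressed mood". Part D asks about improvement in daily life, for example "How do you think your life has improved with respect to your participation in leisure activities". Part E has two overall liking items. A separate 0-10 item under General Comments asks "Overall, how much improvement do you believe occurred, after completing the treatment program".
- **CEQ (Appendix M).** The lead-in asks how far the woman believes "that the therapy you are receiving will help to reduce your anxiety". Four of the six items then name depressive symptoms.
- **TAQ (Appendix K).** The printed response scale runs from 1 to 6, but the column head gives the range 0-6. Item 7 reads "I believe that the techniques used in the program were beneficial".

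**The concern.** Satisfaction and symptom change should be two different things if their correlation is to be informative. Part C asks the woman to rate her own improvement in depressive symptoms, which the EPDS and the DASS depression scale also measure. Part D rates improvement in functioning; its leisure item has a counterpart in WHOQOL-BREF item 14. If these items count as satisfaction, perceived improvement is being correlated with measured improvement for part of the score. A positive result for hypothesis (c) could then not be read as satisfied women doing better. Hypothesis (a) is touched too: a woman who liked the program but did not improve would score as less satisfied.

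The CEQ lead-in names a different symptom from the items below it. Anxiety is a separate outcome in this trial and hypothesis (c) relates expectancy to every outcome, so the form should say one thing throughout.

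**Working it through.** The protocol gives no figure for this correlation and puts no number on a moderate one, so there is nothing to reproduce. The check is a count of the printed items, followed by a bound under stated assumptions.

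**1. Item count (Appendix L, items rated 0-7).** Part A 10, B 12, C 5, D 4, E 2; total 33, maximum 33 × 7 = 231 points.

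- Improvement items (C + D): 9/33 = 27% of items, 63 of 231 points.
- Adding the 0-10 item: 10/34 = 29% of items, 73/241 = 30% of points.
- Part C alone: 5/33 = 15%.
- Parts A + B + E: 10 + 12 + 2 = 24 items.

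**2. Correlation carried by the improvement items alone.** Take an equally weighted total with k improvement items, each correlated r with symptom change, and m = 33 − k other items with zero correlation with change. Let ρ be the inter-item correlation within a block and x the correlation between blocks. With items of unit variance,

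r_total = k·r / √[ m + m(m−1)ρ + k + k(k−1)·max(ρ, r²) + 2mkx ].

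The ranges below are assumptions, not taken from the documents: r from 0.3 to 0.7, ρ from 0.3 to 0.7, x of 0 or 0.3.

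| Case (k = 9, m = 24) | Sum under the root | r_total |
| --- | --- | --- |
| r = 0.7, ρ = 0.3, x = 0 | 189.6 + 44.28 = 233.88 | 6.3/15.29 = 0.41 |
| r = 0.5, ρ = 0.5, x = 0 | 300 + 45 = 345 | 4.5/18.57 = 0.24 |
| r = 0.3, ρ = 0.7, x = 0.3 | 410.4 + 59.4 + 129.6 = 599.4 | 2.7/24.48 = 0.11 |

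Over all 18 combinations the range is 0.11 to 0.41. Four reach 0.30, taken here as the lower edge of moderate. With Part C alone (k = 5, m = 28) the range is 0.06 to 0.21.

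**3. A cruder version as a cross-check.** Treat the nine improvement items as one perfectly correlated block and the other 24 as another, with no correlation between the two: r_total = 9r/√(24² + 9²) = 9r/25.63. For r = 0.5, 0.6 and 0.7 this gives 0.18, 0.21 and 0.25.

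**4. Against statistical significance.** If 58 women are allocated 1:1 with no dropout (assumptions; the protocol states neither), n = 29 in the treated arm and the two-sided 5% critical value is r = 0.367. The cruder figures all lie below it, as do 17 of the 18 combinations in step 2.

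**5. Sensitivity to weighting.** If the five parts were weighted equally, with C and D as one block and A, B and E as the other, r_total = 2r/√(3² + 2²) = 2r/√13, or 0.28 to 0.39 for r from 0.5 to 0.7. Treating all five parts as mutually uncorrelated gives 2r/√5, or 0.45 to 0.63. At r = 0.7, however, that requires two uncorrelated parts jointly explaining 2 × 0.49 = 98% of the variance in change, which is implausible.

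**6. CEQ count.** Of six items, four name depressive symptoms, two (how logical the therapy seems; recommending it to a friend) name no symptom, and none names anxiety. Only the lead-in names anxiety.

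**The case against.** The strongest objection is that the overlap depends on a scoring rule the protocol never states. It names the instrument but does not say that a TSQ total enters the correlation, and the Analysis paragraph does not describe the correlation. The form's five separately instructed parts would equally allow part scores, and an analysis plan not shown here may fix this. That stands, and it is why the point is conditional on the whole form being scored. It does not dispose of the point, because the protocol ties satisfaction to the TSQ as a whole and nothing in it sets the improvement items aside.

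It is also fair that the overlap is uneven. Hypothesis (c) covers anxiety, stress, parenting stress and quality of life as well, whereas Part C concerns depressed mood and negative thoughts. Change scores are not computed from the TSQ, so the link between perceived and measured improvement remains empirical. The expectancy half of the hypothesis has no such overlap.

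Two stronger readings are tempting. A reader might infer that a moderate correlation is all but assured, so that hypothesis (c) could not fail. The figures do not support this: most plausible item totals fall below 0.3, and the high values need equal part weights, which the protocol nowhere states, together with implausibly uncorrelated parts. A reader might also infer that the CEQ measures expectancy about anxiety instead of depression. It does not: every symptom-specific item says depressive symptoms, and the effect of the stray word on scores is probably small.

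**Conclusion.** The point holds in limited form. Nine of the 33 TSQ items rated 0-7, plus the 0-10 item, measure perceived improvement. If the whole form is used as satisfaction, part of its correlation with symptom change comes from shared content. For an item total that part is roughly 0.1 to 0.4, assuming that improvement items correlate 0.3 to 0.7 with change and that the other items are unrelated to it. A moderate correlation is thus not guaranteed, but one that appeared could not be attributed to satisfaction.

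The CEQ lead-in and the TAQ column head are plain inconsistencies on forms that participants read. TAQ item 7 rates the program's techniques in a questionnaire meant for the therapist relationship, but it is one item of 17 and its effect on hypothesis (b) has not been quantified.

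All of this concerns secondary analyses within the treated arm. The randomised comparison of efficacy is untouched.

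**What to change.** - Define satisfaction for hypotheses (a) and (c) as TSQ Parts A, B and E (24 items). Report Parts C and D and the 0-10 item separately as perceived improvement, outside hypothesis (c). This removes the direct improvement items from the satisfaction score. Usefulness ratings may still track benefit, but that is a relation the hypothesis can properly test.
- In the CEQ lead-in, replace anxiety with depressive symptoms so that it agrees with the four symptom-specific items. No item needs changing.
- Make the TAQ column head match the printed 1-6 scale.
- Optionally, repeat the alliance correlation without TAQ item 7 as a sensitivity check.

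The cost is a sentence of scoring and two small form corrections, with no new data. The one drawback is less direct comparability with uses of the full TSQ; showing the full score descriptively beside the restricted one would ease that. The form corrections need to be made before the forms are used, since later scoring cannot repair an instruction already read.

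### With only pre and post scores in both arms, the planned ANOVA efficacy test is a change-score t-test; adjusting for baseline would be at least as precise and usually more so

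*Protocol*

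**What the plan says.** The Analysis paragraph of the protocol's project description fixes the efficacy method: "Treatment efficacy will be determined using repeated measures mixed-model analysis of variances (ANOVAs". It names no covariate. For effect size it says "Eta square effect sizes will be computed for all outcome measures". Simple effects and interaction contrasts appear in the sentence on maintenance of gains: "Mixed-model ANOVAs along with tests of simple effects and interaction contrasts will be computed".

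The term being tested follows from Purpose and Hypotheses, which expects that "TAICBT participants will demonstrate significantly greater symptom and clinical improvement from pre- to post-treatment on all outcome measures". That is a group-by-time interaction, although the Analysis paragraph does not name the term.

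The Method paragraph gives the design: "58 women will be randomized to receive either TAICBT treatment or assigned to a 7-10 week WLC". Apart from three questionnaires given only to the treated arm, it says "All other measures will be completed by both groups of participants at pre-treatment and post-treatment (10 weeks after baseline". The later contact is in one arm only: "TAICBT participants will be contacted by telephone four weeks following treatment completion".

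Section III, item 1 uses EPDS cut-offs, together with the MINI, for eligibility. Section III, items 3 and 4 place the EPDS at the pre-screen. The questionnaire battery comes after random assignment, when the woman has been told her arm.

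**The concern.** Two measurements per woman in each of two arms leave a repeated-measures ANOVA one efficacy contrast: the difference between arms in mean change. A change score in effect fixes the coefficient of the baseline at 1. A regression that estimates the coefficient uses the same data and cannot have larger residual variance, apart from the cost of estimating one more parameter.

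The trial is small and collects the baseline anyway. If the correlation between pre and post scores is moderate and the two SDs are similar, the planned test gives up precision that would otherwise take a materially larger sample to recover.

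**Working it through.** **Inputs.** From the protocol: 58 women, two arms, and two time points common to both. Not in the protocol, so assumed: 1:1 allocation (58/2 = 29 per arm), two-sided 5%, equal pre and post SDs in the main case, and a pre-post correlation rho of 0.3 to 0.7. The figure of 58 cannot be reproduced, because no alpha, power, effect size or SD is stated with it.

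**Identity.** A two-group, two-time split-plot ANOVA was built on simulated data with 29 per arm. F for group by time was 4.9378, equal to t² from the change-score t-test, with 56 error df in both.

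**Variance, equal SDs (SD = 1).** Planned: 2(1 − rho). Baseline-adjusted: 1 − rho². Ratio: (1 + rho)/2. The equivalent gain in sample size is 1/ratio − 1.

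| rho | planned | adjusted | ratio | equivalent extra women | detectable difference at 80% power (SD) |
|---|---|---|---|---|---|
| 0.3 | 1.40 | 0.91 | 0.65 | 54% | 0.89 → 0.71 |
| 0.5 | 1.00 | 0.75 | 0.75 | 33% | 0.75 → 0.65 |
| 0.7 | 0.60 | 0.51 | 0.85 | 18% | 0.58 → 0.53 |

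**Power for 0.6 SD at rho 0.5.** The planned SE is √(2 × 1.00/29) = 0.263, so the noncentrality is 0.6/0.263 = 2.28. The adjusted SE is √(2 × 0.75/29) = 0.227, giving 0.6/0.227 = 2.64. The noncentral t with 56 and 55 df gives 61% and 74%.

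**Cost of adjustment.** The critical t moves from 2.0032 (56 df) to 2.0040 (55 df). Chance baseline imbalance inflates the adjusted variance on average by 55/54. Setting (1 + rho)/2 × 55/54 = 1 gives rho = 0.96, so the cost exceeds the gain only above that. At rho 0.5 the inflation takes about one point off the 74%.

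**Unequal SDs.** With post SD 1 and baseline SD s, the planned variance is 1 + s² − 2·rho·s and the adjusted variance is 1 − rho². The difference is (s − rho)², which is never negative but can be zero. At rho 0.5:
- s = 0.8: 0.75/0.84 = 0.89
- s = 0.6: 0.75/0.76 = 0.99
- s = 0.5: 0.75/0.75 = 1.00, no gain

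At s = 0.6 the ratio is 0.91 for rho 0.3 and 0.98 for rho 0.7.

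**Baseline answered after disclosure.** Suppose knowing the arm shifts one arm's baseline by 0.2 SD and leaves the post score unaffected. With equal SDs, the change score is then biased by 0.20 SD and the adjusted difference by rho × 0.2: 0.06, 0.10 and 0.14 SD at rho 0.3, 0.5 and 0.7. Adjustment is less affected, but not immune.

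**Validity.** Simulated type I error with complete data and rho 0.5 was 5.2% for both analyses.

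**The case against.** The strongest reply is that the planned test is valid, answers the stated pre-to-post hypothesis directly, and contradicts nothing in the protocol. That stands: the point is about efficiency. The headline figures also rest on equal SDs and on correlations that the protocol does not give. That stands too, and is why a range is shown.

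Four stronger readings are tempting, but the document does not support them.

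- A reader might infer that the entry restrictions lower rho and so enlarge the gain. The (1 + rho)/2 formula needs equal SDs, and selecting on the baseline breaks that. A narrower baseline range tends to shrink the gain, as the unequal-SD figures show. This matters mainly for the EPDS, the outcome screened by cut-off.
- A reader might infer that women lacking one score are dropped and that dropout biases the result. The protocol states no analysis set. Eta squared and interaction contrasts suggest the classical ANOVA, but mixed-model could also mean a likelihood model that keeps women with one score. Such detail may sit in an SAP not shown. With complete data the identity holds on either reading, provided baseline means are not constrained.
- A reader might infer that baseline adjustment by itself brings in every randomised woman. It does not: a woman without a post score contributes nothing to that regression unless a missing-data method is added.
- A reader might count eta squared and the baseline tests ("chi-square tests will be conducted to assess for group differences in demographic data and baseline measures") as faults of equal weight. Both are minor. The same paragraph also plans means, SDs, clinical significance, and remission and recovery rates. Because the questionnaire baselines follow disclosure of allocation, differences in them need not be pure chance.

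**Conclusion.** The point holds as an efficiency recommendation. Because only two time points are common to both arms, the planned efficacy test is a change-score t-test. Adjusting for the baseline is at least as precise apart from one degree of freedom, and usually more so. With 29 per arm, two-sided 5% and equal SDs, the saving in variance is 35%, 25% and 15% at rho 0.3, 0.5 and 0.7. All of these conditions are assumptions. The gain could be close to nil on the EPDS if screening narrows its baseline range. The protocol states no entry cut-off on the DASS, PSI-SF or WHOQOL-BREF, so that particular reason for a small gain does not apply to them. The change is worth making because it needs no further participants or measurements. It does not correct an invalid test.

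**What to change.** In the Analysis paragraph, make the efficacy analysis for each outcome a regression of the post-treatment score on assigned arm, with that scale's own baseline as covariate. Report the adjusted mean difference in scale points with a 95% CI; eta squared may stay as a supplement.

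Use the pre-screen EPDS as the EPDS covariate, since it precedes randomisation. For the DASS, PSI-SF and WHOQOL-BREF, do not use a longitudinal model that forces equal baseline means across arms, because those baselines are given after the woman knows her allocation.

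The regression does not settle what happens to women without a post score; the method for them, with its missing-data assumption, can be stated here or in the SAP.

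The cost is about two sentences and one degree of freedom, with the same data and software.
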